# Protocol for a Phase Two, Parallel Three-Armed Non-inferiority Randomized Controlled Trial of Acceptance and Commitment Therapy (ACT-Adjust) Comparing Face-to-Face and Video Conferencing Delivery to Individuals With Traumatic Brain Injury Experiencing Psychological Distress

**DOI:** 10.3389/fpsyg.2021.652323

**Published:** 2021-03-08

**Keywords:** traumatic brain injury, acceptance and commitment therapy, video conferencing, randomized control trial, telehealth, psychological distress

## Abstract

**Background:** People with traumatic brain injury (TBI) face a range of mental health challenges during the adjustment process post-injury, but access to treatment can be difficult, particularly for those who live in regional and remote regions. eHealth provides the potential to improve access to evidence-based psychological therapy for people with a severe TBI. The aim of the current study is to assess the efficacy of a psychological intervention delivered via video consulting to reduce psychological distress in people with TBI.

**Methods:** This paper outlines the protocol for a multi-center, three-arm, parallel, non-inferiority randomized controlled trial (RCT) of an evidence-based manualized psychological intervention, ACT-Adjust. ACT-Adjust provides nine sessions for adults with a moderate to severe TBI experiencing clinical levels of psychological distress. Fifty-six participants referred from Brain Injury Rehabilitation Units across New South Wales (NSW) and the NSW icare scheme will be randomly allocated to three conditions; (1) video consulting (VC), (2) face-to-face (FtF) and, (3) a waitlist control (WL).

**Discussion:** This is the first RCT to evaluate the efficacy of a psychological therapy (ACT-Adjust) delivered via video consulting for individuals with a moderate to severe TBI.

**Trial Registration:**
www.anzctr.org.au, Australian New Zealand Clinical Trials Registry ANZCTRN2619001602112.

## Introduction

Psychological distress following a traumatic brain injury (TBI) is highly prevalent (Gould et al., 2011) and includes mixed mental health problems with features of depression, anxiety, anger, and stress. Whilst first line treatment often involves medication aimed at symptom reduction, this alone does not provide the individual with strategies to address the complex psychological adjustment process following TBI. Psychological interventions utilizing cognitive behavioral therapy (CBT) to ameliorate mental health symptomology tend to be disorder-specific, targeting specific symptoms of hopelessness, anxiety, depression, and anger (Medd and Tate, 2000; Simpson et al., 2011; Hsieh et al., 2012; Fann et al., 2015). Acceptance and Commitment Therapy (ACT) is a transdiagnostic treatment with the therapeutic goal of assisting people in managing their mental health through increased psychological flexibility.

ACT encompasses the six core processes of acceptance, defusion, contact with the present moment, self as context, values identification, and committed action with the central aim of increasing psychological flexibility. Acceptance involves noticing unpleasant or unwanted internal experiences without trying to change or avoid them, while defusion uses a range of experiential exercises to assist in changing the relationship with those unpleasant internal experiences. Being in contact with the present moment allows the person to be aware without judgment and without influencing or changing the experience. Self as context or the observing self, allows the person to see themselves as separate from their thoughts, feelings, and experiences and notice there is a transcendent self that remains the same. Mindfulness exercises are used to assist movement through these processes. Values and committed action constitute the behavioral component of ACT and allows the individual to focus their behavior and set goals in a way that is consistent with their underlying principles. ACT uses experiential exercises and metaphors which can be adapted and applied to individuals who have a cognitive impairment as a result of a TBI (Whiting et al., 2017).

ACT-Adjust is an evidence-based treatment program incorporating the transdiagnostic components of ACT with modifications to account for the cognitive impairments experienced by individuals with a severe TBI (Whiting et al., 2012). It has been specifically designed to facilitate psychological adjustment after a severe TBI. In a recent clinical trial testing the feasibility of the program, ACT-Adjust achieved both statistically and clinically significant reductions in levels of depression and stress amongst clients with a moderate to severe TBI, compared to an active control group (Whiting et al., 2020).

Despite the growing evidence-base for interventions treating psychological distress following a TBI (Medd and Tate, 2000; Simpson et al., 2011; Hsieh et al., 2012; Fann et al., 2015; Ponsford et al., 2016; Abel et al., 2017; Brenner et al., 2018; Dindo et al., 2020; Whiting et al., 2020), access to psychological services is limited for regional and remote people across Australia (Bourne et al., 2017), resulting in high levels of unmet needs (Simpson et al., 2016). eHealth, the provision of healthcare at a distance via technology, has the potential to increase access to services and has seen burgeoning research with a growing evidence base (Backhaus et al., 2012). ACT, for the treatment of a variety of mental health issues, has been delivered in a number of eHealth formats, including online, smartphone applications, and telehealth with positive outcomes (O'Connor et al., 2018). Within the TBI field, reviews have indicated positive effects of eHealth in supporting family members (Rietdijk et al., 2012) and in the provision of interdisciplinary rehabilitation care (Tran et al., 2017; Ownsworth et al., 2020). Although research related to use of eHealth delivery of interventions for people with TBI is limited, one case study design (*n* = 3) found delivery of treatment to address executive functioning via video was feasible on outcome measures of function and satisfaction with delivery method (Ng et al., 2013). Psychological therapy delivered by eHealth (telepsychology) for emotional disorders after a brain injury, however, has been limited to telephone-based counseling and has produced mixed results (Bell et al., 2005, 2011; Bombardier et al., 2009). An initial study comparing telephone delivery of a psychological intervention (motivational interviewing and solution-focused counseling) compared to usual care found significant differences between the groups, where the active condition demonstrated improved functional status and well-being (Bell et al., 2005), however when the study was replicated with a large sample (*n* = 433), no differences were found between the two groups (Bell et al., 2011).

To date, there is no research looking at the efficacy of psychological therapy to treat mental health issues delivered by video consulting to adults with a moderate to severe TBI. The purpose of this paper is to describe the design of a non-inferiority, randomized controlled trial, to examine whether an eHealth-based delivery of the ACT-Adjust treatment program achieves the same treatment effects as face-to-face delivery. It also will examine the efficacy of ACT-Adjust when compared to a wait-list control group and determine whether treatment gains are sustained three months after the intervention.

## Methods and Analysis

### Overview of Study Design and Research Hypotheses

The ACT-Adjust project aims to build on the success of the original feasibility trial (Whiting et al., 2020) and evaluate the benefits of utilizing eHealth for delivery of a psychological intervention to people with a TBI. This pre-registered, multi-center, three-arm, parallel, non-inferiority, single-blind randomized controlled trial (RCT) will test the efficacy of two modes of delivery of the ACT-Adjust intervention; face-to-face (FtF) and video consulting (VC), in comparison to a waitlist control group (see Figure 1).

**Figure 1 F1:**
[figure not shown]
Study flow diagram.

This paper describes the study protocol (Dated September 30, 2019; Protocol Version 1.0) to comply with the Standard Protocol Items: Recommendations for Interventional Trials (SPIRIT) (Chan et al., 2013), see Supplementary Table 1 for Spirit Checklist. The trial will be conducted according to the Consolidated Standards of Reporting Trials (CONSORT) of Electronic and Mobile HEalth Applications and onLine TeleHealth (CONSORT E-HEALTH) statement (Eysenbach, 2011), CONSORT Social and Psychological Interventions (CONSORT-SPI) (Montgomery et al., 2018) guidelines and CONSORT extension for the reporting of non-inferiority trials (Piaggio et al., 2012). The trial has been registered on the Australian New Zealand Clinical Trials Registry (ANZCTRN2619001602112). Refer to Appendix I for more details.

The study will commence immediately following ethics approval and recruitment of participants will continue for ~2 years. The overall duration of the study will be 3 years to allow for those in the wait list control condition to complete the intervention and the follow up assessment, and for data analysis and dissemination of results. To test the efficacy of the intervention, the study will test the following hypotheses:

ACT-Adjust intervention: Participants in the active treatment regardless of delivery (FtF vs. VC) will demonstrate increased psychological flexibility and decreased psychological distress following the intervention, compared to those in the control group (waitlist).eHealth: There will be no differences in primary and secondary outcomes between participants who receive the ACT-Adjust intervention by FtF compared to those who receive it via VC.Sustained treatment effects: Participants in the active treatment condition, ACT-Adjust (VC and FtF), will maintain their gains three months post intervention.

### Participants and Settings

The study will recruit participants with a moderate to severe TBI through the community outpatients service Brain Injury Rehabilitation Program, NSW, Australia (BIRP) (Tate et al., 2004) and through icare, NSW. The BIRP is a network of multidisciplinary team-based, community outpatient services located in both regional and metropolitan areas of the state of NSW, Australia providing brain injury rehabilitation to individuals with a traumatic brain injury. The BIRP service is overseen by Rehabilitation physicians and a client centered approach to rehabilitation is undertaken. icare is a NSW state government organization that provides funding and case management services to individuals who have incurred a catastrophic injury (TBI, spinal cord and multiple limb amputations) as a result of a motor vehicle accident.

### Eligibility Criteria

Inclusion criteria will comprise: (i) having sustained a severe TBI (post-traumatic amnesia =>7 days) after 18 years of age; (ii) being between 18 and 65 years old; (iii) <5 years post-injury; (iv) having sufficient cognitive-linguistic capacity to complete self-report measures and participate in the program; and (v) reporting a clinically significant level of psychological distress (Depression >13, Anxiety >9, and Stress >18; Depression Anxiety Stress Scales 21-item; DASS-21) (Lovibond and Lovibond, 1995). Exclusion criteria are: (i) having a severe psychiatric illness, including psychotic disorder or substance addiction as determined by the medical file, self-report or consultation with the rehabilitation team; (ii) currently receiving a psychological intervention; and (iii) living >1-h travel distance from a psychologist able to deliver the intervention, to ensure access to a psychologist regardless of whether the therapy is delivered FtF or by VC.

### Recruitment Process

Screening will be conducted of individuals within the BIRP and icare services to identify prospective participants for the clinical trial. The following processes will be followed to recruit participants from the respective services:

BIRP: Health professionals employed by NSW Health at each BIRP location will review current clients of the service to assess suitability for the study. Researchers will contact staff at each BIRP to prompt regular reviews of the services' caseloads throughout the duration of the trial. Participants will be initially approached by their contact at the BIRP service either in person or by telephone (usually their case manager) and consent for the research team to contact the participant by phone will be sought. Following verbal consent, a member of the research team will contact participants and provide the participant information sheet and consent form (screen) by mail or email.

icare: Researchers will give a series of presentations to icare teams across NSW to promote the trial and recruitment of participants. Potential clients will be identified by icare case managers by one of two methods:(a) if they score <3 on either items 5 (*How much do you enjoy life?*) or 6 (*To what extent do you feel your life to be meaningful?*) or >3 on item 26 (*How often do you have negative feelings such as blue mood, despair, anxiety, depression?*) on the WHO Quality of Life—BREF measure (WHOQOL Group, 1998), which is administered as routine clinical practice by icare; or (b) by their knowledge of the participant's current situation. The icare staff member will approach the potential participant by telephone for possible involvement in the research and seek consent for the research team to contact the participant directly. Following verbal consent, a member of the research team will contact the participant by phone and provide the participant information sheet and consent form (screen) by mail or email.

### Randomization

The randomization process was performed by a researcher independent of the research team. A computer generated randomization list was generated for each phase of the study using online randomization software, Sealed Envelope (Sealed Envelope Ltd, 2019). The initial randomization had a ratio of 2:3:2 (FtF:WL:VC), with a permuted block size of seven. Following Time 2 Data Collection (13 weeks after Baseline/Time 1), wait list control participants will be randomized to the ACT-Adjust intervention on a ratio of 1:1 (FtF:VC), using a permuted block size of four. The results for both phases were placed in sequentially numbered opaque and sealed envelopes. Following completion of a participant's baseline assessment, the Research Assistant will open the next sequential randomized envelope available to determine the participant's assigned condition. The following allocations are required: ACT-Adjust face-to-face *n* = 16 participants; ACT-Adjust eHealth *n* = 16 participants; Waitlist control *n* = 24 participants.

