Each participant enrolled in the trial will receive a Therapy Kit comprising a hardcopy of the ACT-Adjust 2.0 Client Workbook and individually wrapped materials for Session 2 (Chinese finger trap), Session 5 (packet of sultanas), and Session 6 (values card pack). All participants will complete the ACT-Adjust 2.0 program (Table 1), which is comprised of 9 × 1.5 h sessions. The week prior to commencing the program (and before randomization occurs), participants will meet with the treating psychologist in person to complete Baseline assessments. Sessions 1–7 will occur on a weekly basis, and a 2-week break will be placed between Sessions 7 and 8, and a 4-week break between Sessions 8 and 9. If required, sessions may be rescheduled by arrangement between the participant and treating psychologist, and will be rescheduled as soon after the original session as is feasible. Following the completion of Session 9, participants will meet with an independent blinded assessor to complete the Time 2 assessment measures (within 1 week of treatment completions). Three months after completing Session 9, participants will meet again with an independent blinded assessor to complete Time 3 assessment measures.

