### Informed Consent

During the consent process, all participants will be informed as to the purpose of the research, any potential risks or benefits and processes to withdraw from the study and provided with the Participant Information Sheet (see Supplementary File 2). By definition, clients who have the cognitive capacity to participate in the ACT-Adjust program, will have sufficient cognitive capacity to provide written informed consent. Participants' capacity to provide informed consent will be determined by a review of any available neuropsychological assessment and in consultation with their treating health professionals including their Rehabilitation Specialist. Consent will be fully explained to the participants in simple language and they will be given the opportunity to have a family member present during the consent process. Language will be used at an appropriate level for participants' cognitive impairment and extra time will be provided for participants to process and think about the research. All consent for the trial will be undertaken by the Chief Investigator (DW).

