### Blinding

Psychologists conducting baseline assessments (Time 1) will be blinded to participant treatment allocation, as participants will be randomized after the baseline assessment (Time 1). Blinding of the treating psychologists providing the intervention is not possible, however an independent assessor will be used to complete the post-treatment (Time 2) and 3-month follow-up assessments (Time 3) and will be blinded to the condition. The success of blinding will be assessed by having the independent assessor (i) indicate which condition they think the participant was randomized to (FtF, WL or VC) and (ii) indicate if the participant disclosed their treatment condition. Data analysis will be undertaken by a statistician, from the Ingham Institute for Applied Medical Research but not directly associated with the individual research group, who will be blinded to the treatment conditions. It is not anticipated unblinding will be required for the independent assessor or statistician and therefore is not permissible in this study.

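### Fixed, published block sizes mean that randomizing after baseline does not by itself keep the next allocation unknown to staff who know the earlier ones

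*Protocol article*

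**What the plan says.** The Randomization section describes one list for each phase: "A computer generated randomization list was generated for each phase of the study using online randomization software". It mentions no stratification. For the first phase, "The initial randomization had a ratio of 2:3:2 (FtF:WL:VC), with a permuted block size of seven". After Time 2, "wait list control participants will be randomized to the ACT-Adjust intervention on a ratio of 1:1 (FtF:VC), using a permuted block size of four". An independent researcher produced the lists, and "The results for both phases were placed in sequentially numbered opaque and sealed envelopes". On who opens them: "Following completion of a participant's baseline assessment, the Research Assistant will open the next sequential randomized envelope available".

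The Blinding section says "Psychologists conducting baseline assessments (Time 1) will be blinded to participant treatment allocation", and the only reason it gives is that randomization follows the Time 1 assessment. It also accepts that treating psychologists cannot be blinded while they deliver the intervention. Under Intervention: ACT-Adjust 2.0, the baseline assessor and the therapist are the same person: "participants will meet with the treating psychologist in person to complete Baseline assessments". That section also lists three of the article's authors among the therapists, and the initials show that one of them is the Chief Investigator. Under Informed Consent, "All consent for the trial will be undertaken by the Chief Investigator".

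Appendix I gives March 2020 as first enrolment and the status as recruiting, so the block sizes were published while envelopes remained to be opened.

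**The concern.** A sealed envelope hides the slip inside it. It does not hide what a fixed block must still contain once the earlier slips are known. The last allocation in every block of seven is fully determined by the six before it, and sometimes the sixth or fifth is determined too.

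The people who could hold that information are close to enrolment. The Research Assistant opens the envelopes. The Chief Investigator takes every consent and also treats. Psychologists who do baselines know the arm of the participants they go on to treat. Some therapists are authors of the article that prints the block sizes.

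Foreknowledge would give room for the timing of a consent or baseline visit, or the help given with questionnaire items (the Measures section lets the assessor read them out), to depend on the coming arm. The Data Analysis section measures outcomes relative to pre-treatment levels, so a distorted baseline or selective enrolment could enter both the comparison with waitlist and the comparison of the two delivery modes. Blinded assessment at Time 2 and Time 3 would not undo it.

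**Working it through.** **Inputs.** From the Randomization section: first phase 2:3:2 in blocks of 7, targets 16, 24 and 16; second phase 1:1 in blocks of 4, for the 24 waitlist participants. How much staff know of earlier allocations is not stated, so it is varied below.

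**The plan's own figures.** 56/7 = 8 complete blocks, and 8 × (2, 3, 2) = 16, 24, 16. 24/4 = 6 complete blocks. Both agree with the article.

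**First phase, full knowledge.** An allocation is certain when every slot left in the block belongs to one arm. All 210 orderings of a block are equally likely.
- Slot 7 is always certain: 1.
- Slot 6 is certain if the last two slots match: (1 + 3 + 1)/21 = 5/21 = 23.8%.
- Slot 5 is certain if the last three are all waitlist: 1/35 = 2.9%.
- Expected certain slots per block: 1 + 5/21 + 1/35 = 19/15 = 1.267.
- Share: 1.267/7 = 18.1%. Count: 1.267 × 8 = 10.1 of 56.

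For therapy versus waitlist only (4:3), the expected number per block is 1 + 9/21 + 5/35 + 1/35 = 1.6. That is 22.9%, or 12.8 of 56.

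Enumerating the 210 orderings, the best guess of the exact arm is right 57.5% of the time. Always naming the waitlist is right 3/7 = 42.9% of the time.

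**First phase, partial knowledge.** In simulation, each earlier allocation in the block is known with probability q, and the block position is known.

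| q | Certain share | Of 56 |
|---|---|---|
| 1.0 | 18.1% | 10.1 |
| 0.9 | 11.2% | 6.3 |
| 0.75 | 5.0% | 2.8 |
| 0.5 | 0.8% | 0.5 |
| 0.33 | 0.1% | 0.1 |

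**Second phase, full knowledge.** Per block of four: 1 + 2/6 = 4/3. Share 33.3%; count 4/3 × 6 = 8 of 24. The best guess is right 70.8% of the time, against 50% by chance.

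**Effect of varying block sizes.** This was simulated with sizes equally likely, for an observer who knows all earlier allocations and the set of possible sizes. Blocks of 7 and 14 cut the certain share to about 6% (6.6% with the total fixed at 56, 5.5% on a long list). The best-guess rate moves only from 57% to about 55%. Blocks of 2, 4 and 6 in the second phase cut the certain share from 33% to about 8% with the total fixed at 24, while the best-guess rate stays near 71%.

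**The case against.** The strongest reply is that 18% describes an observer the documents never identify. The Research Assistant, not the psychologist, opens the envelopes. Several therapists work across New South Wales, and a therapist who knows only their own cases could foresee almost nothing. This stands: 18% is a ceiling, and the partial-knowledge rows are nearer to what an individual therapist could do.

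Other inferences that a reader might draw also fail:
- A single list without site strata is not an aggravating feature. Sharing one list across sites makes local prediction harder.
- The trial is not open-label. The article calls it single-blind, with an independently generated, concealed list and blinded assessors at Time 2 and Time 3. What is true is that some staff learn allocations as they occur.
- The identifier file that the Chief Investigator and Research Assistant can access links names to study identifiers. The article does not say that it holds allocations.

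The scope for steering is also limited. Candidates are first approached by rehabilitation or icare staff, distress is judged against fixed DASS-21 cut-offs, and the primary outcomes are self-reported. Bias is therefore possible but not shown, and neither its direction nor its size can be derived.

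None of this rescues the stated reason. That randomization comes later does not prevent prediction, and no section separates those who consent or assess from the running allocations.

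**Conclusion.** The point holds in limited form. The ground given for baseline blinding is insufficient, because a fixed and published block of seven lets a person with full knowledge of earlier allocations foresee up to about 18% of first-phase allocations (10.1 of 56). This rests on knowing every earlier allocation, the block position and the block size; with less knowledge the share drops quickly. The main exposure is the Research Assistant, and the Chief Investigator if allocations are shared.

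A reader might infer that baseline blinding fails for roughly one participant in five. The documents do not support that, since nothing gives baseline psychologists the sequence. Nor does the block of four weaken Time 1 blinding, because it operates only after Time 2. Its 8 of 24 is a separate matter of concealing the second randomization. This is a cheap improvement to concealment, not evidence that the trial's comparisons are biased.

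**What to change.** 1. From the next complete block in each phase, have the independent researcher regenerate the unopened envelopes with randomly varying block sizes, for example 7 and 14 at 2:3:2, and 2, 4 and 6 at 1:1. Constrain the remainder so that the totals stay at 16:24:16 and 12:12. Do not disclose the sizes to the Research Assistant, the Chief Investigator or the therapists.
2. Keep the running allocation log from anyone who takes consent or does baseline assessments. This matters at least as much as step 1, because varying the sizes removes most certain predictions but hardly lowers the success rate of an informed guess.
3. Amend the Blinding section to say that baseline blinding depends on this concealment as well as on the order of events.

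The cost is a constrained re-run of the list by the same independent researcher, refilled envelopes and a short amendment. Arms may be slightly uneven if recruitment stops mid-block. Predictability is reduced, not removed.
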